#### Variation of power (phase 2)

The aim of phase 2 is to determine the best power/irradiation time (Watts/s) for use on humans to enhance muscle recovery following physical exercise. For such, the dose with the best results in phase 1 will be used and the same methodological and evaluative measures will be employed. Thus, only the power of the equipment (and consequently irradiation time) will be varied (100, 200, 400 or 0 mW). As energy (E) expressed in Joules is equal to power (P) expressed in Watts multiplied by time (t) measured in seconds, different power variations will lead to the same total energy delivered to the tissue. *A priori*, if the best dose were determined to be 10 J, the following would be the parameters:

•10 J = 0.1 W (100 mW) × 100 s

•10 J = 0.2 W (200 mW) × 50 s

•10 J = 0.4 W (400 mW) × 25 s

•10 J = 0.0 W (placebo, 60 s)

### Isokinetic protocol: eccentric contractions

Precisely 3 minutes after the end of LLLT, the volunteers will perform the eccentric contraction protocol, which will consist of 75 eccentric isokinetic contractions of the knee extensor musculature in the non-dominant leg (five sets of 15 repetitions, 30-second rest interval between sets) at a velocity of 60°.seg^-1^ in both the eccentric and concentric movements with a 60° range of motion (between 90° and 30° of knee flexion). At each contraction, the dynamometer will automatically (passively) position the knee at 30°; the dynamometer will then flex the knee until reaching 90°. The volunteers will be instructed to resist the knee flexion movement imposed by the dynamometer with maximum force. Instructions on how to execute the maneuver will be given first and the volunteers will receive verbal encouragement throughout the protocol. Despite the diversity of protocols proposed for the execution of eccentric exercises on isokinetic dynamometers, the protocol described here was chosen based on a previous study carried out [28] in which this method proved effective and reproducible for the exercise-induced muscle damage.

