**Design and methods:**

A double-blind, randomized, placebo-controlled clinical trial with be conducted. After fulfilling the eligibility criteria, 28 high-performance athletes will be allocated to four groups of seven volunteers each. In phase 1, the laser power will be 200 mW and different doses will be tested: Group A (2 J), Group B (6 J), Group C (10 J) and Group D (0 J). In phase 2, the best dose obtained in phase 1 will be used with the same distribution of the volunteers, but with different powers: Group A (100 mW), Group B (200 mW), Group C (400 mW) and Group D (0 mW). The isokinetic test will be performed based on maximum voluntary contraction prior to the application of the laser and after the eccentric contraction protocol, which will also be performed using the isokinetic dynamometer. The following variables related to physical performance will be analyzed: peak torque/maximum voluntary contraction, delayed onset muscle soreness (algometer), biochemical markers of muscle damage, inflammation and oxidative stress.

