#### Stretching and warm-up

Prior to the isokinetic protocol, the volunteers will perform three 60-second sets of active stretching of the knee extensors of the non-dominant lower limb. The volunteers will then perform a warm-up exercise consisting of pedaling a stationary bike (Inbramed, Porto Alegre, RS, Brazil) at 100 rpm for 5 minutes without load.

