#### Isokinetic protocol: maximum voluntary contraction (MVC)

An isometric dynamometer will be used for the evaluation of muscle function and the execution of the exercise protocol. This instrument is considered the method with the greatest reliability for the measure of the musculoskeletal performance. Immediately after the stretching and warm-up exercises, the maximum voluntary contraction (MVC) test will be performed. For such, the volunteers will sit on the seat of the isokinetic dynamometer (System 4, Biodex Medical Systems, Inc., Shirley, NY, USA) with an angle of 100° between the trunk and hip and the non-dominant leg positioned with the knee at 60° of flexion (0° corresponds to complete knee extension) and attached to the seat of the dynamometer by a strap. The dominant leg will be positioned at 100° of hip flexion and will also be attached to the seat by a strap. The volunteers will also be attached to the seat of the dynamometer through the use of two straps crossing the trunk. The volunteers will be instructed to cross their arms over the trunk and the axis of the dynamometer will be positioned parallel to the center of the knee. The MVC test will consist of three 5-second isometric contractions of the knee extensors of the non-dominant leg. The highest torque value of the three contractions (peak torque) will be used for the statistical analysis. The choice of this parameter is due to the fact that this variable reflects the maximum generation of force by the muscle. Instructions on how to execute the test will be given first and the volunteers will receive verbal encouragement during the execution of the test. This test has demonstrated reliability and reproducibility in a previous study carried out [28]. The MVC will be performed immediately (1 minute) after the eccentric contraction protocol as well as 1, 24, 48, 72 and 96 hours after the eccentric contraction protocol to evaluate post-exercise muscle recovery.

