#### Variation of dose (phase 1)

In phase 1, the output power will be fixed at 200 mW and LLLT will be applied 2 minutes prior to the pre-exercise MVC test with the cluster in direct contact with the skin at six distinct sites of the knee extensor musculature of the non-dominant limb (two medial, two lateral and two central sites). As the cluster has five diodes and six different sites will be irradiated, a total of 30 points will be irradiated in the musculature. Based on the results of the randomization, the volunteers of the four experimental groups will receive the following doses: Group A, 2 J per diode, 10 J on each application of the cluster with 200 mW (10 seconds of irradiation at each site), 60 J of total irradiated energy on the muscle (60 seconds of total irradiation time); Group B, 6 J per diode, 30 J on each application of the cluster with 200 mW (30 seconds of irradiation at each site), 180 J of total irradiated energy on the muscle (180 seconds of total irradiation time); Group C, 10 J per diode, 50 J on each application of the cluster with 200 mW (50 seconds of irradiation at each site), 300 J of total irradiated energy on the muscle (300 seconds of total irradiation time); and Group D, 0 J per diode (placebo) (20 seconds of irradiation at each site, 120 seconds of total time, but without effective irradiation).

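### Timing before the eccentric bout is fixed only from the end of the laser, so the minimum time since warm-up depends on the arm (4 to 8 minutes in phase 1)

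*Protocol article*

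**What the plan says.** All references are to the protocol article.

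- **Stretching and warm-up:** three 60-second sets of stretching, before the isokinetic protocol. "The volunteers will then perform a warm-up exercise consisting of pedaling a stationary bike", "at 100 rpm for 5 minutes without load".
- **Isokinetic protocol: MVC:** "Immediately after the stretching and warm-up exercises, the maximum voluntary contraction (MVC) test will be performed".
- **Abstract, Design and methods:** the isokinetic test is based on "maximum voluntary contraction prior to the application of the laser and after the eccentric contraction protocol", which puts the first MVC ahead of the laser.
- **Variation of dose (phase 1):** "LLLT will be applied 2 minutes prior to the pre-exercise MVC test", which puts it after the laser. Total laser time over six sites is 60 s (2 J), 180 s (6 J) and, for 10 J, "300 J of total irradiated energy on the muscle (300 seconds of total irradiation time"). The sham lasts 120 s.
- **Variation of power (phase 2):** irradiation time changes with power. The worked example, conditional on 10 J being the best dose, begins "10 J = 0.1 W (100 mW) × 100 s" and goes on to 50 s at 200 mW, 25 s at 400 mW and 60 s for placebo.
- **Isokinetic protocol: eccentric contractions:** "Precisely 3 minutes after the end of LLLT, the volunteers will perform the eccentric contraction protocol".

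No section ties the bout, or the start of the laser, to the end of the warm-up.

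**The concern.** The warm-up exists to bring the muscle to a standard state before testing and exercise. If the laser comes after it, and the bout is timed only from the end of the laser, an arm with longer irradiation goes into the bout longer after warming up. The treatment assignment sets that difference. Randomisation therefore cannot balance it, and the planned repeated-measures ANOVA cannot separate it from dose or power among the active arms. It would remain even if blinding were perfect.

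At stake is the comparison of doses in phase 1, because the dose with the best results is carried into phase 2, and then the comparison of powers. The placebo does not give a neutral reference: in phase 1 its sham time lies between those of the active arms.

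**Working it through.** **Step 1. Reproduce the stated laser times.** Time per site = energy per diode / power; total = 6 sites × time per site.

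- 2 J: 2 / 0.2 = 10 s; × 6 = 60 s
- 6 J: 6 / 0.2 = 30 s; × 6 = 180 s
- 10 J: 10 / 0.2 = 50 s; × 6 = 300 s
- Placebo: 20 s × 6 = 120 s

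All four match the article.

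**Step 2. Where the laser must fall.** Stretching takes 3 × 60 = 180 s and cycling 5 × 60 = 300 s, together 480 s. Only 180 s separate the end of the laser from the bout. Neither the whole preparation nor the cycling alone fits, so the laser comes after the warm-up. This holds whether the first MVC precedes the laser (Abstract) or follows it (phase 1 section).

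**Step 3. Minimum warm-up-to-bout interval, phase 1.** Laser time + 180 s, ignoring moves between sites and any MVC time outside the 180 s.

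| Arm | Laser or sham (s) | + 180 s | Minutes |
|---|---|---|---|
| 2 J | 60 | 240 | 4 |
| Placebo | 120 | 300 | 5 |
| 6 J | 180 | 360 | 6 |
| 10 J | 300 | 480 | 8 |

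Among active arms laser time is exactly 30 s per joule (60/2 = 180/6 = 300/10), so its correlation with dose is 1.0. With placebo included it is 0.90, because 0 J has a longer time than 2 J. The sham is 60 s longer than 2 J, 60 s shorter than 6 J and 180 s shorter than 10 J.

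**Step 4. Phase 2.** Total laser time = 6 × dose / power.

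| Dose carried forward | 100 mW | 200 mW | 400 mW | Active-arm spread |
|---|---|---|---|---|
| 2 J | 120 s | 60 s | 30 s | 90 s |
| 6 J | 360 s | 180 s | 90 s | 270 s |
| 10 J | 600 s | 300 s | 150 s | 450 s |

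Time is exactly inverse to power in each row. At 10 J, adding 180 s gives 780, 480 and 330 s, that is 13, 8 and 5.5 min. The placebo figure depends on how its 60 s is read. Per site, like the other lines of the example, it is 6 × 60 + 180 = 540 s (9 min). As a total it is 60 + 180 = 240 s (4 min).

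**Step 5. The pre-exercise MVC.** If it precedes the laser, straight after the warm-up, the laser does not affect it. If it follows the laser by 2 minutes, the interval must run from the end of the laser: counted from the start, irradiation would still be in progress for 6 J (180 s) and 10 J (300 s). The minimum warm-up-to-MVC interval is then laser time + 120 s: 180 s (2 J), 240 s (placebo), 300 s (6 J) and 420 s (10 J). That cannot be squared with an MVC straight after the warm-up.

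**The case against.** The case against is substantial.

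- **These are minimums.** No section says how soon after the warm-up the laser starts. They become actual differences only if every arm starts equally promptly. Where the MVC comes first, a wait before the laser would contradict nothing in the warm-up or eccentric sections. A full protocol might contain such a wait, and the Figure 1 flowchart is not shown. This stands, and the point is stated conditionally.
- **No harm is quantified.** The article gives no rate at which warm-up is lost. Multiplying minutes by an assumed percentage of torque would produce a figure with no basis in the document, and zero cannot be excluded. This stands.
- **The path to the outcome is indirect.** Post-exercise MVC is measured from 1 minute to 96 hours after 75 eccentric contractions. Time since warm-up can reach it, and the damage markers, only by altering the bout. The pre-exercise MVC is exposed only if it follows the laser, and in that case the MVC contractions themselves come shortly before the bout, at the same lag in every arm. This stands.
- **Irradiation time is part of what is studied.** Phase 2 varies power and time together on purpose. That is true, but time since warm-up is a further difference, and a wait can separate it from irradiation time.
- **The defect in the text is the contradictory session order.** That must be settled first. But step 2 shows that neither order takes the laser out of the gap between warm-up and bout.

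**Conclusion.** The point holds as a minor design fix. The stated times force the laser between warm-up and bout, and the only fixed clock starts when the laser ends. Given an equally prompt laser start in all arms, the minimum interval since warm-up is 4, 5, 6 and 8 min for 2 J, placebo, 6 J and 10 J. In phase 2 the active arms differ by up to 90, 270 or 450 s, depending on the dose chosen. Among active arms the interval is completely confounded with dose or power.

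A reader might infer three stronger things that the document does not support:

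- **That the dose ranking is biased by some percentage of peak torque.** Neither size nor direction can be computed, and the effect may be small.
- **That the interval follows dose across all four arms.** It does not, since placebo lies between 2 J and 6 J in phase 1.
- **That every phase 2 arm necessarily differs.** If 6 J were chosen and a 60 s per-site sham kept (an assumption), placebo and 100 mW would tie at 360 s of laser or sham time. The three active arms would still differ.

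**What to change.** 1. Reconcile the Abstract with the sections on warm-up, MVC, phase 1 dose and eccentric contractions, so that they give one order of warm-up, MVC and laser.
2. Within each phase, hold the interval from the end of warm-up to the start of the eccentric bout the same in all arms, set by the longest arm. Shorter arms wait before the laser starts. The 3-minute laser-to-bout interval, the doses and the powers do not change.
3. If the reconciled order puts the pre-exercise MVC after the laser, its interval from warm-up should also be equal in all arms. Step 2 achieves this if the MVC keeps a fixed lag from the end of the laser. The wording that places the MVC straight after the warm-up must then be reconciled with it. If the MVC comes first, the wait goes between MVC and laser.
4. State whether the 60 s phase 2 sham is per site or in total.

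**Cost.** In phase 1 the waits are 480 − 240 = 240 s (2 J), 480 − 300 = 180 s (placebo) and 480 − 360 = 120 s (6 J), so at most 4 min. In the 10 J phase 2 example the longest wait among active arms is 780 − 330 = 450 s (7.5 min). For placebo it is 240 s if the sham is per site, or 780 − 240 = 540 s (9 min) if the 60 s is a total. The shorter arms go into the bout somewhat longer after warm-up than they otherwise would. No athletes or equipment are added, and the researcher who programs the device already knows the allocation and can call the laser start.

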### Data analysis

The intention-to-treat analysis will be followed. The primary outcome will be peak torque obtained from MVC at different time-points. Secondary outcomes will be biochemical markers CK, LDH, IL-1β, IL-6, TNF-α, TBARS, carbonylated proteins, CAT and SOD.

Data will be expressed as mean and standard deviation and will be firstly tested regarding normal distribution using Shapiro–Wilk test. ANOVA test with repeated measurements for the time factor will be performed to test between-groups differences (followed by the Bonferroni post hoc test). The level of significance for the statistical analysis will be set at 5% (*P* ≤0.05).

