### Calculation of sample size

The sample size was calculated based on a previous study [28], in which a similar experimental model and exercise protocol was employed as that to be used in the proposed study. The sample size calculation considered a β of 20% and α of 5%. In the study used as reference for this calculation of Baroni *et al*. [28], LLLT led to the post-exercise recovery of creatine kinase (CK) (muscle injury marker) to 435.95 U/l (standard deviation: 238.04), whereas placebo treatment led to an increase in CK to 1,327.58 ± 949.82 U/l. Using these parameters, a total of seven volunteers would be needed for each of the four groups in each phase of the study (total of 28 volunteers per phase).

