## Discussion

In the proposed study, the ideal LLLT application dose and power will be identified and the long-term effects of LLLT on post-exercise muscle fatigue and musculoskeletal recovery will be evaluated. For such, evaluations will be carried out of peak torque during MVC, late-onset muscle pain will be determined and biochemical analyses will be performed to determine changes in markers of inflammation, oxidative stress and muscle damage. The inflammatory process is known to be a defensive reaction against injury. This process has been extensively studied in its different aspects. Briefly, the main inflammation events are: 1) tissue injury; 2) the release of vasoactive substances by the injured tissue; 3) vasodilatation; 4) leukocyte adherence; 5) the migration of leukocytes from the blood stream to the injury site; and 6) tissue repair. Thus, muscle inflammation is a natural consequence of exercise-induced muscle damage [30].

Over time, LLLT exhibits a biphasic, dose–response pattern. This means that intermediate doses within a ‘therapeutic window’ trigger stimulation effects in biological tissue, whereas doses outside this range do not trigger any effects [31-34]. However, the therapeutic window varies depending on the condition to be treated [31]. Likewise, the power and irradiation time employed are extremely important to obtaining the best results. Thus, a short irradiation time and an output power that is either too low or too high can lead to null results [31,34]. Our intention, therefore, is to determine ideal laser therapy application parameters capable of slowing down the physiological muscle fatigue process, reducing injuries or micro-injuries in skeletal muscle stemming from physical exertion and accelerating post-exercise muscle recovery. We believe that, unlike drug therapy, LLLT has a biphasic dose–response pattern.

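### The stated 80% power belongs to CK, LLLT versus placebo; it does not cover the primary outcome (peak torque) or comparisons between active doses or powers

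*Protocol article*

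**What the plan says.** Calculation of sample size (protocol article) sets beta at 20% and alpha at 5% and takes its inputs from one earlier study with a similar exercise model. On the active side, "LLLT led to the post-exercise recovery of creatine kinase (CK) (muscle injury marker) to 435.95 U/l", with an SD of 238.04; on the other, "whereas placebo treatment led to an increase in CK to 1,327.58 ± 949.82 U/l". From these it concludes that seven volunteers per group are needed, 28 per phase. No other outcome or contrast enters the calculation.

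Data analysis states: "The primary outcome will be peak torque obtained from MVC at different time-points". It continues: "Secondary outcomes will be biochemical markers CK, LDH" and seven further markers. The planned test is a repeated-measures ANOVA with Bonferroni post hoc comparisons.

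The aim is comparative among active arms. The Abstract seeks the best dose and the best power/irradiation time. Variation of power (phase 2) carries the best-performing phase 1 dose forward. The Discussion says that "the ideal LLLT application dose and power will be identified".

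**The concern.** The article contains one power statement, and it rests on a secondary outcome and on active versus placebo. Nothing links it to peak torque or to differences among 2, 6 and 10 J, or among 100, 200 and 400 mW. A reader who takes the 20% beta as the power of the trial could treat a null torque result, or a failure to separate the active arms, as adequately powered evidence of no difference. The sample size section gives no support for that reading. It matters here because the phase 1 result fixes the dose used in phase 2, and because the article promises to identify the ideal parameters.

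**Working it through.** **Inputs from Calculation of sample size.** CK means 435.95 and 1,327.58 U/l; SDs 238.04 and 949.82; alpha 0.05 (sidedness not stated, two-sided assumed); power 0.80; n = 7 per group.

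**1. Reproducing the plan's figure.**
- Difference: 1,327.58 − 435.95 = 891.63 U/l.
- Simple mean of the SDs: (238.04 + 949.82)/2 = 593.93, so d = 891.63/593.93 = 1.50.
- n per group = 2(1.960 + 0.842)²/1.50² = 6.97, rounded up to 7. Power at n = 7 is 0.802 (normal approximation).

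Seven is therefore a two-group CK calculation without multiplicity adjustment. It depends on averaging two very unequal SDs: the root-mean-square SD, 692.39, gives d = 1.29 and 10 per group.

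**2. The same CK contrast under the planned post hoc adjustment.** Four groups give 4 × 3/2 = 6 pairs, three of them active versus active. At alpha 0.05/6 = 0.0083, power for d = 1.50 and n = 7 falls to 0.57, and 11 per group would be needed for 80% (normal approximation).

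**3. Peak torque.** No difference or SD is given, so no required n can be computed. What can be computed is the difference detectable with 80% power at n = 7, in SD units, for one time-point without baseline adjustment (non-central t, non-centrality d√(7/2)):

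| Error df | Unadjusted | Bonferroni, six pairs |
|---|---|---|
| 12 (the two groups only) | 1.63 | 2.18 |
| 24 (all four groups) | 1.56 | 2.01 |

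Baseline and repeated measurements reduce these. Assume equal correlation r between all MVC tests, adjustment for one baseline, and the mean of six post-exercise tests as response. The SD is then multiplied by √[(1 + 5r)/6 − r²], and the 24-df values become (the one df spent on the covariate is ignored):

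| Assumed r | Multiplier | Unadjusted | Bonferroni |
|---|---|---|---|
| 0.5 | 0.58 | 0.90 | 1.16 |
| 0.7 | 0.51 | 0.80 | 1.02 |
| 0.8 | 0.44 | 0.69 | 0.88 |

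The article gives no correlation, so these rows only show the range. They refer to a difference averaged over the six tests, not to one time-point.

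Power at one time-point for assumed torque effects (normal, unadjusted, n = 7): 0.5 SD gives 0.15, 0.8 SD gives 0.32, 1.0 SD gives 0.46 and 1.5 SD gives 0.80.

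**4. Active versus active, on CK.** No such difference is given either. Suppose two doses differ by half the LLLT–placebo gap, 445.8 U/l. Unadjusted power at n = 7 (normal approximation) is:
- 0.29 with SD 593.93 (d = 0.75), the SD that reproduces the plan;
- 0.23 with SD 692.39 (d = 0.64);
- 0.94 if both active arms had the LLLT SD of 238.04 (d = 1.87).

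The answer turns on inputs that the article does not supply.

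**The case against.** The sample size section is open about its basis: it names CK, labels the two arms and gives all the figures, and it nowhere claims 80% power for torque. That stands. The fault is a mismatch between sizing outcome and primary outcome, not concealment.

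A reader might go further and infer that the trial is underpowered for its primary outcome. The document does not support this. It gives no torque effect or SD, and the 1.6 to 2.2 SD values describe a single time-point, whereas the plan is a four-group repeated-measures analysis. With baseline adjustment and high within-person correlation, the detectable difference could be about half as large. One caution applies to that gain: the Abstract places the MVC test before the laser, whereas Variation of dose (phase 1) places the laser before the pre-exercise MVC test. The two must be reconciled before that test is treated as a pre-treatment baseline.

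It is also fair that taking the best dose into phase 2 is a selection, which need not require a significant pairwise test. Power to reject equality is not the probability of choosing the best arm, and that probability is not assessed here.

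None of this supplies a link from the CK calculation to the primary outcome or to the active-versus-active aim.

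**Conclusion.** The point holds as a mismatch. The only stated power, 80%, belongs to an unadjusted comparison of CK between LLLT and placebo at d = 1.50. It would carry over to peak torque, or to one dose against another, only if that difference were also about 1.5 SD under the same simple calculation, and the article gives no ground for assuming so. Even for CK it falls to 57% under the planned Bonferroni adjustment.

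Whether n = 7 is too small for torque or for separating the active arms is undetermined. The torque effects, the correlations and the halved CK gap used above are assumptions shown as ranges. Nor is seven an arithmetical error: it reproduces, although only with the averaged SD and the normal approximation.

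**What to change.** 1. In Calculation of sample size, state that the 80% power refers only to CK, LLLT versus placebo, before Bonferroni adjustment, and that n was not derived for peak torque or for dose-versus-dose or power-versus-power contrasts.
2. For the primary outcome, give instead the difference in peak torque detectable with seven per group under the planned analysis, as a range over stated assumptions. For one time-point without baseline adjustment this is about 1.6 SD unadjusted and 2.0 to 2.2 SD with Bonferroni over six pairs; add the smaller values under baseline adjustment and repeated measures, with the assumed correlation beside each. Convert to N·m only if the sponsor holds a torque SD; the article does not report one.
3. In Data analysis, report active-versus-active differences with confidence intervals, and state that non-significance does not show that doses or powers are equal.
4. In the Discussion, soften the statement that the ideal dose and power will be identified, to match.

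The cost is a less favourable power statement. The primary outcome, the planned test and the group size stay as they are, and no athletes are added.

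### Run on complete cases, the planned repeated-measures ANOVA would drop any athlete with one missed reading; a mixed model on all readings fits the stated intention-to-treat aim better

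*Protocol article*

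**What the plan says.** The Data analysis section of the protocol article makes two commitments in close succession. The first is the principle: "The intention-to-treat analysis will be followed". The second is the method: "ANOVA test with repeated measurements for the time factor will be performed to test between-groups differences", with Bonferroni comparisons afterwards.

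The same section defines the primary outcome as a series rather than a single value: "The primary outcome will be peak torque obtained from MVC at different time-points". The section on the isokinetic MVC protocol gives the schedule. There is a test after stretching and warm-up, before the eccentric exercise, and then "The MVC will be performed immediately (1 minute) after the eccentric contraction protocol as well as 1, 24, 48, 72 and 96 hours". That makes seven readings per athlete, four of which (24, 48, 72 and 96 h) fall on later days. The blood markers follow the same seven-point schedule.

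The section on sample size arrives at seven athletes in each of four groups, 28 per phase, and states no allowance for loss. The article does not say how an incomplete series is to be treated, nor by what estimation method the ANOVA is to be fitted.

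**The concern.** The classical repeated-measures ANOVA works on a full row of readings per participant. If a row has a gap, the usual procedure removes the whole row. An athlete who attends everything except the 72 h test would then contribute nothing to the peak torque analysis, although six of his seven readings are valid. An analysis restricted to complete attenders is not an analysis of all randomised athletes, so the named method is an awkward partner for the declared principle.

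The small groups make this matter more. One athlete is 1/7, or 14%, of a group. The nine blood markers are separate outcomes, so a lost sample would not affect peak torque, but different outcomes could end up resting on different sets of athletes. Phase 1 also selects the dose carried into phase 2, so precision lost in phase 1 bears on that choice.

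**Working it through.** **1. The plan's own figure.** Inputs from the section on sample size: CK 435.95 U/l (SD 238.04) with laser, 1,327.58 U/l (SD 949.82) with placebo, α 5%, power 80%. The article does not state sidedness; two-sided is assumed here.

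- Difference: 1,327.58 − 435.95 = 891.63.
- Simple average of the SDs: (238.04 + 949.82)/2 = 593.93.
- n per group = 2 × (1.960 + 0.842)² × (593.93/891.63)² ≈ 6.97, rounded up to 7.

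This reproduces the stated 7. With the root-mean-square SD (692.39) the same formula gives 10. The averaged SD is used below only because it matches the plan. There is no margin for loss in the 7.

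**2. What one gap does.** A constructed data set of 28 athletes × 7 readings = 196 values had one value removed.

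| Analysis | Athletes kept | Readings kept |
|---|---|---|
| Repeated-measures ANOVA, complete cases | 27 | 27 × 7 = 189 |
| Mixed model, all available readings | 28 | 195 |
| Univariate split-plot linear fit, all available readings | 28 | 195 |

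Deletion therefore belongs to the complete-case form of the method. It is not unavoidable under the name repeated-measures ANOVA.

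**3. How many athletes could be lost.** The article gives no missed-visit rate. Assume that each of the four 24–96 h readings is missed independently with probability p. The probability of a full series is (1 − p)⁴, and the chance that all 28 are complete is that value to the power 28.

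| p per visit | (1 − p)⁴ | Expected complete of 28 | Average per group | Chance all 28 complete |
|---|---|---|---|---|
| 0% | 1.000 | 28 | 7 | 100% |
| 1% | 0.961 | 26.9 | 6.7 | 32% |
| 3% | 0.885 | 24.8 | 6.2 | 3% |
| 5% | 0.815 | 22.8 | 5.7 | under 1% |
| 10% | 0.656 | 18.4 | 4.6 | under 1% |

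**4. What that costs in power, on the only planning figures available.** These are for CK, a secondary outcome; the article gives none for peak torque. The normal approximation is power = Φ(891.63 / (593.93 × √(1/n₁ + 1/n₂)) − 1.960).

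- 7 and 7: 80.2%.
- 7 and 6: Φ(891.63/330.43 − 1.960) = Φ(0.738) ≈ 77.0%.
- 6 and 6: 73.9%.
- 5 and 5: 66.0%.

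**5. Bias.** An illustrative simulation assumed a difference of about 5 MVC points, a between-athlete SD of 8, a within-athlete SD of 5, and later readings missed more often after a larger 24 h deficit. Complete-case differences were 4.81 and 4.69 against a true 5.03, shortfalls of 0.22/5.03 = 4.4% and 0.34/5.03 = 6.8%. On the same inputs, the standard error of a single-time difference with seven per group is √(8² + 5²) × √(2/7) ≈ 5.0 points. The bias is thus about 4–7% of one standard error, and towards no effect. Every input here is assumed.

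**The case against.** A reader might infer that the plan contradicts itself: that any missed visit will remove the athlete and that intention-to-treat is therefore not delivered. The article does not support this. It nowhere provides for deleting incomplete series. Imputation before the ANOVA, or a split-plot fit to the available readings, would keep all 28 athletes, and the intention-to-treat sentence itself points away from silent deletion. Rules for missing data are commonly left to a full protocol or analysis plan, which is not shown, so their absence here is no fault. All of that stands.

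Nor does the article show that gaps are likely. It describes one professional team, a minimum of 80% participation in practice sessions, and only four days of follow-up. It is plausible that the sorest players would skip late tests after 75 maximal eccentric contractions, but this is not documented. The simulated bias rests on invented inputs and is small beside sampling error, so it cannot carry the point.

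What remains is the choice of model, which the article does fix. The alternatives that rescue the ANOVA are workarounds: imputation needs values supplied for the missing readings, and with unequal numbers of readings per athlete the between-group F-test of a split-plot fit is no longer exact. A mixed model needs neither.

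The exclusions for injury or changed practice routine during the study also sit uneasily with intention-to-treat and need reconciling with it. That is a separate matter: settling it would not keep an athlete who merely missed the 72 h test.

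**Conclusion.** The point holds conditionally. If the ANOVA is run in its standard complete-case form and readings are missed, the analysis of that outcome would not cover all randomised athletes. Under independent misses at the four later visits, the expected number of complete athletes is 24.8, 22.8 or 18.4 of 28 per phase at 3%, 5% or 10% per visit. The rates are assumptions, and with complete data the effect is nil. The loss is chiefly one of athletes and precision: on the CK figures, going from 7 to 6 in both groups of a comparison lowers power from 80.2% to 73.9%. This is an inexpensive improvement to a method the article has named, not an error that invalidates the plan.

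**What to change.** In Data analysis, replace the repeated-measures ANOVA by a linear mixed model for repeated measures:

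- fixed effects for group, time and group-by-time;
- a random effect for athlete, or a simple covariance structure fixed in advance;
- REML estimation with Kenward-Roger degrees of freedom;
- fitted to every available reading of every randomised athlete.

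Add that an athlete who misses a visit is still measured at the remaining ones, and that no reading is discarded because another is missing.

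The cost is about one sentence and standard software, with no extra athletes or visits. With complete data and a random intercept, the model gives the same group and group-by-time tests as the planned ANOVA (without a sphericity correction, and provided the estimated between-athlete variance is positive). The one downside is having to choose the covariance in advance. It should be simple: an unstructured matrix for seven readings has 7 × 8/2 = 28 parameters, as many as there are athletes. The model protects against gaps that depend on observed readings; it does not cure gaps that depend on unobserved ones.
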